### Procedure for unblinding if needed {17b}

The sponsor personnel will analyze data semi-blinded (groups 1–2–3) and only unblind after completion.

## Data collection and management

### Plans for assessment and collection of outcomes {18a}

Risk-based monitoring of the trials shall be conducted by qualified and experienced CRAs and shall be in accordance with a Monitoring Plan that clearly describes the strategy, methods, responsibilities, and requirements for monitoring the trials.

In accordance with applicable regulations, GCP, and ISGlobal procedures, CRAs shall meet with the site prior to the start of the study to review with the site staff the protocol and their responsibilities to satisfy regulatory, ethical, and ISGlobal requirements. When reviewing data collection procedures, the discussion shall also include training on the electronic source requirements, entry into the clinical trials’ database, as well as access and security procedures.

The investigator and the head of the institution (where applicable) agrees to allow the monitor direct access to all relevant documents. The investigator must ensure the provision of reasonable time, space, and qualified personnel for monitoring visits.

As the trials make use of electronic source reporting, most data will be monitored remotely, and queries will be resolved electronically to reduce monitoring time on site.

Upon completion or premature discontinuation of the study, the CRA will conduct site closure activities with the investigator and site staff in accordance with applicable regulations, GCP, and ISGlobal SOPs.

### Plans to promote participant retention and complete follow-up {18b}

Data from withdrawn participants is to be included in the analysis outside explicit requirement. In cases of voluntary discontinuation, it should be established whether consent remains for sample storage. Should the consent be withdrawn, the stored sample will be destroyed and the withdrawal noted in the source notes and CRF. The site shall send a sample destruction letter to the laboratory for actioning. The laboratory shall return a copy of the completed destruction letter once the sample has been destroyed.

### Data management {19}

Data will be collected through a comprehensive electronic data capture (EDC) system with digital data entry forms deployed and stored on the broad OpenHDS (Health and Demographic System). Specifically, the study questionnaires will be designed and deployed on the Open Data Kit (ODK) platform running on the open-source Android operating system. Data transfer from mobile devices (tablets) to servers will be executed using ODK-Collect and Mirth. Data validation will take place both at (a) point of entry via restricted and confirmatory steps, and (b) on the server, via aggregate-level quality checks and alerts. Backups of both the raw input data and the processed data will be stored on the main project server as well as at each site. An audit trail/log of all data modifications, both in terms of inputs and edits, will be generated automatically and available to RAs or authorized study team members upon request.

Every effort will be made to ensure the protection of participant data. In general terms, this means that no identifying data will be transferred to any server unless both (a) its transfer falls within the scope of the project’s protocol, and (b) it is appropriately encrypted and secure.

Paper-based source (e.g., hospital records) will be scanned into the safety database locally and entered into the trials´ databases. Paper-based records will redact all personal identifiers of the participant (e.g.; name of the participant, address or telephone number, hospital file number) and will be stored securely at the site.

Clinical data management shall be performed in accordance with applicable ISGlobal standards and data cleaning procedures.

While completed eCRFs are reviewed by ISGlobal Clinical Research Associates both remotely and at the study site, omissions or inconsistencies detected by subsequent eCRF review may necessitate clarification or correction of omissions and inconsistencies with documentation and approval by the investigator or an appropriately qualified designee. In all cases, the investigator remains accountable for the study data.

The investigator will be provided with a physical data drive (in form of CD-ROM, USB, or HDD) of the final version of the data generated by the project once the database is archived and the study report is complete and approved by all parties. The physical data drive will be compliant with international requirements for data storage and retrieval.

### Confidentiality {27}

Every effort shall be made to protect participant privacy and confidentiality to the extent permitted by law. All trial-related information shall be stored securely at the trial site.

All paper-based participant information shall be stored in lockable file cabinets in areas with access limited to trial staff. Data collection, process, and administrative forms, laboratory specimens, and other reports shall be identified by a coded number only, to maintain participant confidentiality. Participant identifiers (PID) shall contain the number of the trial site and the individual participant number allocated at randomization.

All records that contain names or other personal identifiers, such as locator forms, participant identification code list and informed consent forms, shall be stored separately from study records identified by code number. Only the trial health-care personnel directly responsible for the participant’s care and one designated data management member of staff shall have access to these records.

All databases shall be secured with password-protected access systems.

If the participant’s name appears on any other document (e.g., pathologist report), it shall be obliterated before a copy of the document is supplied to ISGlobal.

Participants’ study data, as identified by PID number only, shall not be released without the participant’s written permission, except as necessary for review and monitoring by:

•Authorized study representatives

•Local and international RAs

•IECs/ IRBs

•Sponsor Monitors

•Sponsor and third-party Auditors

When the results of the study are published, the participant’s identity shall remain confidential

### Plans for collection, laboratory evaluation and storage of biological specimens for genetic or molecular analysis in this trial/future use {33}

Blood samples will be stored in the clinical trial sites in silica gel as a desiccant in −20°C freezers and/or 4°C fridges according to the specific requirements of the processing lab. Samples to be sent to Basel Hospital (Switzerland), KEMRI (Kenya) and ISGlobal (Spain) will be stored separately in different bags, each identified with the corresponding identification number.

Samples may be stored by ISGlobal or its contractor/s for a period of 5 years. The samples will be stored in an accredited, secure, access-controlled laboratory. The samples will be identified by a participant ID and visit code until the end of the trials where after which they will be delinked so that they cannot be linked to a specific participant. Additional research regarding the use of ivermectin to control malaria may be conducted to evaluate hypotheses generated during data analysis, i.e., if a direct effect of ivermectin on the parasite is suspected based on epidemiological results. This includes parasite genetics, serological and immune response to the malaria parasite, and NTDs. Additional uses could include re-analyses with methods being developed during the course of the study, and to answer follow-up questions posed by stakeholders.

The positive RDTs will not be discarded. They will be stored at −20° for 5 years for the conduct of malaria transmission studies (parasite genetics) relevant to the study site (Mopeia). These studies are not part of the BOHEMIA clinical trial and will have independent protocols and approvals for their conduct

## Statistical methods

### Statistical methods for primary and secondary outcomes {20a}

Baseline characteristics in the intervention groups will be compared and assessed for similarity.

The primary outcome of these trials should be the incidence across 6 months of follow-up.

This study comprises three data collection strategies: at the community level with a pediatric active cohort and cross-sectional surveys, and at the health facility level with a passive surveillance system. The main analysis will be conducted at the community level and some secondary and exploratory outcomes will be assessed at the health facility level.

#### Analysis variables

Key analysis variables consist of baseline socio-demographic characteristics, malaria infection incidence (efficacy), and AEs and SAEs data (safety).

##### Efficacy analysis

The primary analysis will be the differential malaria incidence after the 6-month follow-up period between the intervention and control groups. Incidence will be based on monthly RDT results from the active cohort. Each RDT performed will be taken to represent one visit, which is equivalent to one child-month at risk. In the per-protocol correction, 14 days of time at risk for each treatment received (based on the post treatment prophylaxis provided by AL).

Differential incidence between intervention and control clusters will be assessed using a count data regression model accounting for the cluster design effect. Primary analysis will be assessed using generalized estimating equations.

Analysis in the multivariate model will be adjusted for potential confounders identified in the univariate analysis. Based on previous vector-control trials, the variables to be considered can be classified in the following categories: demographics (age and gender), socio-economics (head of household formal education, head of household occupied as a subsistence farmer, electricity in the household, livestock-human ratio, number of nets owned and distance to the nearest health facility), clinical (having experienced fever in the previous 48h, having slept under a bed net the previous night and infection of a sibling in the same household). A step-wise approach will be applied for building the final multivariate model, considering those variables with p-values lower than 0.20 in the univariate analysis.

To assess the bias due to LTFU, sensitivity analyses limited to participants who receive all treatments may be performed. Additional support will be obtained from a comparison of the baseline characteristics of individuals who remain vs. those that are LTFU.

Assessment of the direct benefit to the population that receives treatment will be done through passive surveillance at health facilities and cross-sectional studies to allow for a better risk-benefit analysis in this population.

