#### Efficacy

Infection incidence in the most vulnerable age group (children under 5 years of age) for 6 months from the moment of the first MDA round in their community.

Infection incidence has been chosen as the primary endpoint based on the WHOs PPC for endectocides, which states that in areas of moderate to high transmission, the minimally acceptable efficacy criterion would be “at least 20% reduction in the incidence of clinical malaria (as primary outcome) and incidence of infection (as secondary outcome) in children under 5, lasting for at least 1 month following a single regimen.” The monthly frequency of visits has been chosen given that infected children will receive treatment with Coartem (artemether-lumefantrine), which has an established post-treatment prophylaxis period of 2 weeks [50, 51], monthly visits will allow for at least 14 days at-risk between visits.

Infection incidence will be determined in a cohort of children in the target age that is followed prospectively for 6 months post-receipt of the first dose in the community by a dedicated field team. Each child will be tested at home using RDTs (Parasite Lactate Dehydrogenase (pLDH) and HRP2 based). Two different tests will be used given the known persistence of HRP2 antigen after treatment with up to 50% residual positivity after 6 weeks while LDH-based tests become negative in just 48 h [52]. Quality control of RDT results will include PCR assessment of 10% of the samples.

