## Participant timeline {13}

**Table Tabb:** 

Procedures in treatment/safety cohort	Census and clustering Months −10 to −4	Treatment enrollment visit 1–30 days before dosing	Study visit 1(S) Day 1	Study visit 2(PK) Day 2	Study visit 3(S) Day 3 +/−1 day	Study visit 4(S) Day 6 +/− 1 day	Study visit 5(S) Day 31 +/−3 days	Study visit 7(S) Day 36 +/−1 day	Study visit 8(S) Day 61 +/-3 days	Study visit 10(S) Day 66 +/−1 day	Final safety visit 11(S) Day 91 +/−1 day	End of passive safety surveillance Day 365+/−3 days	Final pregnancy safety visit(S) ^d^ Day 371 +/−3 day
Informed consent census *(separate protocol)*	X												
Demographic data collection	X												
Cluster randomization	X												
Informed consent for treatment		X					X^e^		X^e^				
Complete visit template		X	X	X	X	X	X	X	X	X	X		X
Anthropometry		X					X		X				
Assessment of selected NTDs ^a^		X^a^					X^a^		X^a^		X^a^		X^a^
COVID response^a^		X					X		X		X		X
Review of infant vaccination card (if applicable)		X					X		X		X		
Collection of pharmacology samples ^a^			X	X	X								
Collection of parasite response samples ^b^			X				X		X				
Urine pregnancy test ^c^			X				X		X		X		
Administer study intervention			X				X		X				
Review of side effect personal diary						X		X		X			
Passive surveillance of side effects				X------------------------------------------------------------------------------X									
Adverse event review and evaluation				X-------------------------------------------------------------------------------------------------X									
Active pregnancy surveillance							X		X		X	X	X
Passive pregnancy surveillance (health facility)							X--------------------------------------------------------------------------------X						

^a^Randomly selected sub-sample

^b^Randomly selected sub-sample of children under 5 that also receive treatment (>15 kg)

^c^In participating female participants aged 13-49

^d^Only pregnancies occurring post-treatment

^e^Only subjects not previously enrolled

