## Assignment of interventions: allocation

### Sequence generation {16a}

Once all clusters in the district are defined, the target sample will be randomized using a computer-generated algorithm. Clusters will be randomized 1:1:1 into three study arms. The treatment status of each cluster will be assigned during cluster delineation and then transmitted to the population during a randomization ceremony

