## Trial status

Protocol version 4.2 dated 13 March 2022. Recruitment started on 15 March 2022 in Mozambique. Recruitment was completed in July 2022. Follow-up of the active pediatric cohort will continue until October 2022. Follow-up of the pregnancy cohort will continue until March 2023

We submit the protocol after finishing recruitment but before the completion of the follow-up of the last patient envisioned for March 2023. This is mentioned in the structured summary and is because of the following reasons:

Delayed ethical approval given discussions between the WHO ethics committee and that of Mozambique which were only solved the day before implementation.Implementation difficulties such as floodings, a cholera outbreak and rumors for the first 4 months required the full attention of the study team.The Tanzanian government issued a stop work order for the district of Rufiji given the potential this meant that the team had to seek an alternative site while implementing in Mozambique. This has been found in Kenya and the protocol is currently undergoing review there.

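### Cluster follow-up windows start about 3 to 7 weeks apart in a seasonal disease, yet the primary model's stated covariate list and selection rule leave out calendar time

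*Protocol article*

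**What the plan says.** All references are to the protocol article.

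- **Time origin.** Under Outcomes {12}, Efficacy, infection incidence in children under five is counted "for 6 months from the moment of the first MDA round in their community". The pediatric cohort schedule under Participant timeline {13} ends at day 181 (±3 days).
- **Dates.** Under Trial status: "Recruitment started on 15 March 2022 in Mozambique"; "Recruitment was completed in July 2022"; "Follow-up of the active pediatric cohort will continue until October 2022".
- **Season.** The Discussion describes malaria as seasonal. The Background lists timing relative to the transmission season among the variables that determine the impact of ivermectin MDA.
- **Allocation.** Under Sequence generation {16a}: "Clusters will be randomized 1:1:1 into three study arms". No order in which clusters start is described.
- **Primary model.** The Efficacy analysis section specifies a count regression fitted by GEE on monthly RDT visits. Of the adjusters it says "the variables to be considered can be classified in the following categories: demographics (age and gender), socio-economics", names individual items in each category and adds a clinical group. A step-wise build takes forward variables with univariate p below 0.20. Visit month, season and cluster start date are not listed.

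**The concern.** With a cluster-specific time origin, two clusters that start a month apart contribute child-months from different stretches of the season. This matters in two ways.

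1. **Precision.** Even if start dates are balanced across arms, seasonal differences between clusters add to between-cluster variation, which the sample size sets at a CV of 0.35. A calendar term would remove much of that part.
2. **Possible bias.** Start date is realised after allocation. The arm is known before rollout, field workers are unblinded, and one arm has an additional livestock operation. If one arm started later on average, the seasonal shift would be read as treatment effect or would mask it. The stated model has no term to correct this, and a calendar term added as one more candidate could still be dropped by the p<0.20 screen.

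**Working it through.** **Step 1. Reproduce the planned sample size.** Inputs from Sample size {14}: λ0 = 4.20, λ1 = 3.36 per child-year, k = 0.35, 80% power, 5% significance (taken as two-sided), 14 completers per cluster for 0.5 year, so y = 7 child-years.

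Unmatched-rates formula: c = 1 + (1.96 + 0.842)² × [(λ0 + λ1)/y + k²(λ0² + λ1²)] / (λ0 − λ1)²

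- Variance term: 7.56/7 + 0.1225 × (17.64 + 11.29) = 1.080 + 3.544 = 4.624
- c = 1 + 7.849 × 4.624 / 0.7056 = 52.4, rounded up to 53 per arm, or 159 in total, as stated.
- Power at 53 per arm: Φ(√(52 × 0.7056/4.624) − 1.96) = Φ(2.817 − 1.96) = 80.4%.

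**Step 2. Spread of efficacy starts.** Day 181 is 180 days after the start.

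- A start on 15 March 2022 reaches day 181 on 11 September.
- Follow-up ending 1 October implies a last start on 4 April, 20 days after 15 March.
- Follow-up ending 31 October implies a last start on 4 May, 50 days after 15 March.

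The spread is therefore 20 to 50 days, about 3 to 7 weeks (17 to 53 days with the visit window). This takes 15 March as the first treatment round. If the first round came some days after recruitment opened, the spread is shorter by those days.

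**Step 3. Added variance.** No seasonal amplitude is given, so assume incidence changes by d = 10%, 20% or 30% per month and starts are uniform over m months (30.4 days each). The SD of the log rate is −ln(1 − d) × m/√12, and k′ = √(0.35² + SD²). Power then follows as in Step 1.

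| Spread | d | SD of log rate | k′ | Power |
|---|---|---|---|---|
| 20 days | 10% | 0.020 | 0.351 | 80.3% |
| 20 days | 20% | 0.042 | 0.353 | 80.0% |
| 20 days | 30% | 0.068 | 0.356 | 79.3% |
| 50 days | 10% | 0.050 | 0.354 | 79.8% |
| 50 days | 20% | 0.106 | 0.366 | 77.7% |
| 50 days | 30% | 0.169 | 0.389 | 73.7% |

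A second model gives a similar picture. It uses a sinusoidal 12-month season with amplitude 0.3, 0.5 or 0.8, six-month window means and the least favourable peak. Power is 80.3/80.2/79.6% at 20 days and 79.9/78.8/75.6% at 50 days.

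**Step 4. A lag in one arm (hypothetical).** The shift for a two-week later mean start is 1 − (1 − d)^(14/30.4) = 4.7%, 9.8% and 15.1%. The sinusoidal model gives 4.8%, 8.4% and 15.3%. If the later arm were an intervention arm and incidence were falling, a true rate ratio of 0.80 would appear as 0.80 × 0.953 = 0.76 to 0.80 × 0.849 = 0.68.

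**Step 5. Chance imbalance only.** If start order is unrelated to arm, the SD of the log rate ratio from this source is the SD in Step 3 × √(2/53). At 50 days this is 0.010, 0.021 and 0.033.

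**The case against.** **Randomisation protects against bias.** Clusters are randomised, so start date is independent of arm in expectation unless rollout depended on arm. Nothing in the article says that it did. Floods and bad roads are not specific to an arm, and no text says livestock treatment delayed the human round. Chance imbalance is part of the cluster-level error that the GEE accounts for, and Step 5 shows it is small. This stands: a reader might infer that the trial is biased by season, and the document does not support that.

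**The spread is bounded.** From "Recruitment started on 15 March 2022 in Mozambique. Recruitment was completed in July 2022" a reader might infer starts spread over 4.5 months, or over at least seven weeks. Neither follows. A cohort child starting on 31 July would reach day 181 on 27 January 2023, against a stated end in October 2022. The recruitment sentence names no population. The treatment cohort schedule allows consent at rounds 2 and 3 ("Only subjects not previously enrolled"), and cross-sectional participants are enrolled as well. A round-3 entry on 1 July points to a first round on 2 May, with day 181 on 29 October, which fits. Entry on 1 July to a survey at about day 91 points to a first round near 2 April, 18 days after 15 March. Seven weeks is thus roughly the maximum.

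**The variance may already be counted.** The 0.35 was back-calculated from an earlier cluster trial in the same district and may include some variation in timing. This stands, and it makes the Step 3 losses upper values under each assumption.

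**The SAP or full protocol may cover it.** A calendar term or a rollout order may be specified there. That weakens any complaint about the unstated start order. It does not fully answer the point on the model, because the article itself names the covariates and fixes the selection rule for the efficacy model.

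**Conclusion.** The point holds as a moderate, inexpensive improvement to the stated primary model. Firm from the document: a cluster-specific time origin, a disease described as seasonal, efficacy starts about 20 to 50 days apart, and a named covariate list with a p<0.20 screen that omits calendar time.

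The size rests on an assumed 10-30% monthly change in incidence. The precision cost runs from almost nothing to about 7 power points (80.4% to 73.7% in the most extreme case), and is less if k = 0.35 already contains such variation. Bias is conditional only. A two-week difference in mean start between arms would shift a rate by about 5-15%, which is material against a 20% target, but no such difference is reported. What can be said is that the stated model would not correct one if it occurred.

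**What to change.** - **Model.** Before the analysis team is unblinded, prespecify calendar month of the RDT visit as a fixed term in the primary GEE for all arm contrasts, exempt from the p<0.20 screen. The article says the team was still blinded and data collection was ongoing at submission, so this could be done credibly.
- **Reporting.** Tabulate Day 1 dates of clusters by arm, so that any lag is visible.
- **Rollout.** Recruitment in Mozambique is complete, so start order there cannot be changed. At the Kenya site, not yet started, first rounds can be run in batches with equal numbers from each arm and the order within batches drawn at random.

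The model change needs no new data, because the monthly visits are dated. March to October is eight calendar months, so it costs at most seven extra parameters; sparse end months can be merged. The term assumes a broadly common seasonal pattern across clusters, so it removes most rather than all of the effect. Batching in Kenya affects only team routing.

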### Trial design {8}

The BOHEMIA clinical trial has been designed in accordance with VCAG recommendations for conducting Phase III trials of traditional vector control tools in two different epidemiological settings [43]. The trial will use ivermectin as a first-in-class complementary vector control product to target residual transmission.

The clinical trial will be open-label, superiority, cluster randomized, controlled, parallel arm trial and will last one year. Given the nature of endectocides, which provide indirect protection through a community effect, the intervention must be randomized in clusters.

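### The adjusted efficacy model may select fever and sibling infection as confounders without limiting them to pre-intervention values; follow-up values would pull the incidence ratio toward 1

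*Protocol article*

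**What the plan says.** All of the following is in the protocol article.

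- **Outcome and model.** Efficacy analysis: "Incidence will be based on monthly RDT results from the active cohort", analysed with a count regression that allows for clustering. It adds: "Primary analysis will be assessed using generalized estimating equations".
- **Adjustment.** The same section continues: "Analysis in the multivariate model will be adjusted for potential confounders identified in the univariate analysis". The candidates fall into demographic, socio-economic and clinical groups. The last group reads "clinical (having experienced fever in the previous 48h, having slept under a bed net the previous night and infection of a sibling", where the sibling shares the child's household.
- **Selection.** "A step-wise approach will be applied for building the final multivariate model, considering those variables with p-values lower than 0.20 in the univariate analysis".
- **Timing.** No measurement time is given for the three clinical variables. Analysis variables uses the word baseline only for the socio-demographic characteristics: "Key analysis variables consist of baseline socio-demographic characteristics, malaria infection incidence (efficacy), and AEs and SAEs data (safety"). The paediatric cohort table under Participant timeline {13} has a visit template and an RDT at Day 1 and at each of the six later visits.
- **Mechanism.** Trial design {8} describes endectocides as products "which provide indirect protection through a community effect".
- **Target.** The primary research question (Background and rationale {6a}) asks for a 20% reduction in infection incidence. Sample size {14} uses 4.20 against 3.36 per child-year.

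**The concern.** A confounder in a randomised comparison is at most a chance imbalance in something fixed before the intervention. The three clinical variables are defined relative to a visit, and visits occur monthly throughout follow-up, so the text allows follow-up values.

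- **Fever** at a follow-up visit is partly caused by the infection that the RDT detects. Stratifying on it is stratifying on a consequence of the outcome.
- **Sibling infection** at a follow-up visit is the trial outcome in another child in the same household and cluster. The intervention is meant to work by lowering infection across the community, so holding sibling infection constant removes part of the effect. It also stands in for the cluster's transmission level.
- **The screen** admits variables because they predict the outcome, and consequences of the outcome predict it well.

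At stake is the size of the estimated effect. An intervention that truly meets the 20% criterion could appear to fall short of it if the adjusted figure is the one reported.

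Previous-night net use is different. It is a behaviour, not a result of transmission. The only concern is that a follow-up value is recorded after an allocation that is announced to the population (Sequence generation {16a}) in an open-label trial (Who will be blinded {17a}), so it could differ by arm.

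**Working it through.** **1. Reproduce the design.** Inputs from Sample size {14}: λ0 = 4.20, λ1 = 3.36, k = 0.35, 14 children completing per cluster (20 eligible less 3 and 3), 0.5 year of follow-up, 80% power, 5% significance (taken as two-sided). Child-years per cluster: y = 14 × 0.5 = 7. The Hayes–Bennett formula for unmatched rates is

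c = 1 + (1.96 + 0.84)² × [(λ0 + λ1)/y + k²(λ0² + λ1²)] / (λ0 − λ1)²

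- (4.20 + 3.36)/7 = 1.08
- 0.1225 × (17.64 + 11.29) = 3.54
- (0.84)² = 0.7056

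With unrounded normal quantiles c = 52.43, so 53 per arm and 159 in total, as stated. Power at 53 per arm is 80.4%. The covariate question does not alter the sample size.

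**2. Fever alone, by hand.** Monthly probability of a positive RDT: 4.20/12 = 0.35 in control and 3.36/12 = 0.28 in intervention, ratio 0.80. Assume fever in 40% of RDT-positives and 10% of negatives (the documents give no figures).

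| | Control | Intervention |
|---|---|---|
| Fever and positive | 0.35 × 0.4 = 0.140 | 0.28 × 0.4 = 0.112 |
| Fever, total | 0.140 + 0.65 × 0.1 = 0.205 | 0.112 + 0.72 × 0.1 = 0.184 |
| No fever and positive | 0.210 | 0.168 |
| No fever, total | 0.795 | 0.816 |

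The Mantel–Haenszel ratio across fever strata is

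[0.112 × 0.205/0.389 + 0.168 × 0.795/1.611] / [0.140 × 0.184/0.389 + 0.210 × 0.816/1.611] = (0.0590 + 0.0829)/(0.0662 + 0.1064) = 0.82.

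The ratio moves from 0.80 to 0.82 with nothing to confound. In control children, positivity is 0.140/0.205 = 0.68 with fever and 0.210/0.795 = 0.26 without, a ratio of 2.6. A screen at p<0.20 would very probably keep such a variable.

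**3. Both variables, by simulation.** One intervention arm against control, 53 clusters per arm, 7 households of 2 enrolled children, 6 monthly visits, cluster CV 0.35, true ratio 0.80. Analysis: Poisson GEE, independence working correlation, covariates entered visit by visit, 300 replicates per row. Fever rates, household CV and sibling pairing are assumptions.

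| Fever if positive / negative | Household CV | Unadjusted | + sibling | + fever | + both |
|---|---|---|---|---|---|
| 20% / 5% | 0 | 0.802 | 0.811 | 0.812 | 0.821 |
| 20% / 5% | 0.5 | 0.812 | 0.841 | 0.822 | 0.850 |
| 20% / 5% | 0.8 | 0.825 | 0.871 | 0.834 | 0.877 |
| 40% / 10% | 0 | 0.805 | 0.815 | 0.827 | 0.836 |
| 40% / 10% | 0.5 | 0.806 | 0.835 | 0.827 | 0.853 |
| 40% / 10% | 0.8 | 0.826 | 0.871 | 0.844 | 0.885 |

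At household CV 0.8, capping of high monthly probabilities lifts even the unadjusted ratio above 0.80, so those rows show direction more than size. Rejection rates with both variables differ from unadjusted by at most about 2 points (for example 0.78 to 0.76). Net use at 70%, unrelated to arm, changed nothing.

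**4. Sensitivity to sibling frequency and timing.** A separate simulation (same clusters and CV, 14 children per cluster, household log-SD 0.2–0.47, 150 replicates) gave:

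- every child with an enrolled sibling, follow-up values: 0.80–0.81 becomes 0.82–0.86
- about 43% of children with one (assumed), follow-up values: 0.79–0.81 becomes 0.81–0.84
- Day 1 values of the same variables: no change (within 0.001)

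**The case against.** The strongest reply is that the article never says these are follow-up values. Day 1 is also a visit, with a template and an RDT, so all three variables could be baseline measurements, and step 4 shows that these do no harm. This stands as a limit on the point: the defect is the missing restriction, not a declared plan to adjust for post-randomisation data. It does not remove the point, because the wording is relative to a visit, visits recur monthly, and the article labels other variables as baseline but not these.

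Other replies stand in part.

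- The variables are candidates for selection, not fixed terms. The p<0.20 screen makes this a small comfort for fever and sibling infection.
- The article does not settle the data structure. One count per child over six months also fits its wording, and a visit-level fever has no direct place there. The sizes above apply to visit-by-visit entry.
- Bias toward 1 cannot create a false claim of efficacy, and the superiority test is nearly unaffected.

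A reader might also infer that adjusting for previous-night net use removes part of the effect. The documents do not support this: net use does not result from transmission, no figure shows that it differs by arm, and participants are told only that they take one of two anthelminthics. Nor do they support the inference that the adjusted model will be the headline result, since Efficacy analysis does not say which GEE gives the primary estimate.

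**Conclusion.** The point holds in a limited form. The covariate rule permits adjustment for a symptom of the outcome and for the same outcome in a household member, and its selection method favours both. If follow-up values are used, the direction was toward 1 in every scenario run. With no to moderate household clustering, a ratio of about 0.80–0.81 becomes about 0.81–0.86, so a reduction near 20% would be reported as roughly 14–19%.

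That range rests on assumed fever rates, household variation and sibling frequency, and on covariates entered visit by visit. A single figure for the loss of effect would claim more than the documents allow. If Day 1 values are used, there is no shift. The harm is to the estimate compared with the 20% criterion, not to power. For net use, the concern is only a possible difference by arm after allocation is known.

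This is a stated rule rather than detail left to the SAP. Methods for additional analyses {20b} refers only additional analyses to that document.

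**What to change.** In the protocol's Efficacy analysis section, and in the SAP to match:

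1. Restrict adjustment to a prespecified list of covariates measured at or before Day 1. The listed demographic and socio-economic variables can serve if taken at that time.
2. Drop follow-up fever and follow-up sibling infection from the candidate set.
3. Use previous-night net use only at its baseline value.
4. Replace step-wise selection on univariate p-values with the prespecified list.
5. State whether the unadjusted or the baseline-adjusted GEE is the primary estimate.

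The cost is wording only: no new data and no change to the 159 clusters. The article reports that data collection was ongoing and the analysis team blinded at submission. A change documented before unblinding would be credible.
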